## 7.4. Sample size calculations

This is a non-inferiority trial. Power calculations are made based on non-inferiority calculations. Based on our retrospective data, the absence of death/retransplantation within a year was 90%. We have calculated power to exclude a difference in the primary outcome of 10%, which is the benefit that may be relevant since patients can be transplanted earlier and more patients can be transplanted. We expect that 20% of the transplantations will come from hearts with dysfunction. The power calculation says then that we need 445 transplanted hearts and at least 89 transplanted hearts with dysfunction. Since we do not know the exact incidence, outcome, or transplantation frequency of hearts with dysfunction in a prospective cohort, we primarily plan to include 500 heart-transplanted patients in the study.

To be able to answer our specific research questions about the heart donors, we estimate that we need at least 100 donors of hearts with dysfunction to be able to have a representative group. With an estimated incidence of cardiac dysfunction in 25% of the donors, at least 400 possible heart donors are needed in the study. However, the study intends to continue collecting data from all donors until the primary objective is answered.

## 7.5. Interim analysis (if relevant)

Interim analysis will be performed after 100 patients have been analyzed for the primary outcome and then after every 50 patients who have been analyzed for the

primary outcome. Criteria for stopping the study are a confirmed overrepresentation of primary outcome variables in the group of patients who received a heart from a donor with impaired cardiac function. Overrepresentation must be at least 10 absolute percent in the primary outcome measure as well as show statistical significance ( $p < 0.05$ ) for the study to be terminated. An increased incidence of SAE of at least 20 absolute percent as well as statistical significance ( $p < 0.05$ ) can result in termination of the study.

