### 6.1.2. Serious Adverse Event, SAE

Serious unwanted events include conditions that require more invasive measures or death. SAE include:

- Need of postoperative mechanical assistance more than 24 hours post-op
- Death within 28 days from transplantation
- Other event that resulted in prolonged care time or suffering for the patient (e.g., stroke with sequelae) that can be attributed to, or is suspected to be attributable to, cardiac function of the donor

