## 6.2. Assessment of adverse events

### 6.2.1. Assessment of causal relationship

We believe that AE and SAE will be difficult to attribute to cardiac function of the organ donor. Each SAE in particular will be analyzed in the case there may be a causal relationship with the cardiac function of the organ donor. The incidence of AE and SAE between groups will be analyzed in interim analyses.

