## 6.3. Reporting and registration of adverse events

### 6.3.1. Reporting of adverse events (AE)

AE will not be reported (see above).

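### The SAE comparison that can stop the study counts one class of events by its attribution to donor heart function, the variable that defines the groups; the repeated looks at p < 0.05 are a smaller, separate issue

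*Protocol*

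**What the plan says.** **Looks and thresholds.** Protocol 7.5: "Interim analysis will be performed after 100 patients have been analyzed for the primary outcome and then after every 50 patients". For the primary outcome the condition is double: "Overrepresentation must be at least 10 absolute percent in the primary outcome measure as well as show statistical significance". The level, "statistical significance ( $p < 0.05$ ) for the study to be terminated", is the same at every look, and neither the test nor its sidedness is named. A second limb concerns safety: "An increased incidence of SAE of at least 20 absolute percent as well as statistical significance". Meeting that limb can, but need not, end the study (7.5; 6.4 is also permissive). Section 7.3 prescribes Bonferroni-Holm wherever multiplicity arises and does not mention the looks.

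**What counts as an SAE.** Section 6.1.2 lists three classes. Two need no judgement of cause: mechanical assistance beyond 24 hours after surgery, and death within 28 days. The third takes in other events that prolong care or cause suffering, such as stroke with sequelae, but only if the event "can be attributed to, or is suspected to be attributable to, cardiac function of the donor".

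**How SAEs are used.** Section 6.2.1: "The incidence of AE and SAE between groups will be analyzed in interim analyses". The same section expects attribution to donor heart function to be difficult. Section 6.5 states that the study is neither blinded nor randomized and plans no independent committee.

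**AEs.** Section 6.1.1 defines none, and 6.3.1 says "AE will not be reported (see above").

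**The concern.** A between-group comparison of event rates is interpretable only if an event has the same chance of being counted in each group. For the third SAE class the inclusion test is suspected relation to donor cardiac function. Section 7.2.1 defines the groups by that same variable (regional hypokinesia and/or ejection fraction below 50%). A reporter who knows that the donor heart was impaired has an evident reason to suspect it; a reporter who knows that it was normal has little. The exposure is thus built into the outcome count. Neither more patients nor a smaller p-value removes a bias of this kind.

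At stake is a safety signal that could help to end a study meant to show that these hearts can be used, with no independent body to question how the events were counted.

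The second issue is that p < 0.05 at each of many looks does not describe the chance that the rule as a whole stops the study wrongly. The third is that 6.2.1 promises an AE comparison for which no data will exist.

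**Working it through.** **Inputs from the protocol.** 20% of transplants with impaired hearts; 90% free of events at one year, so a 10% event rate; 10-point margin; 445 patients with at least 89 impaired, 500 planned (all 7.4). Looks and thresholds from 7.5.

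**Plan's own figure.** Alpha and power are not stated. With one-sided 0.025, 80% power and a 1:4 ratio,

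n(impaired) = (1.960 + 0.842)² × 0.10 × 0.90 × (1 + 1/4) / 0.10² = 88.3, rounded up to 89; n(normal) = 4 × 88.3 = 353.2, rounded up to 354.

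The total is 443 against the stated 445, so the 10% rate, 10-point margin and 20% share are the right inputs.

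**Number of looks.** 100, 150, 200, 250, 300, 350, 400: 7 before 445. Inclusion to 500 adds 450, making 8.

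**Primary-outcome limb.** Simulation: 20% impaired, 10% events in both groups, stop when the excess is at least 10 points and two-sided p < 0.05 in the harm direction, 7 looks.

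| Rule | False harm stop | Stops if truth is 20% vs 10% |
|---|---|---|
| As written, chi-square | about 7% | about 67% |
| As written, Fisher | about 5.5% | about 65% |
| Fisher at 0.02 per look | about 3% | about 56% |

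Independent runs of the rule as written gave 7.0-7.8% (chi-square) and 5.4-6.1% (Fisher). The first look alone gives 3.3-3.8% by chi-square and 2.6% by Fisher, so repetition roughly doubles the rate. At that look, with about 20 impaired and 80 normal recipients, 6/20 (30%) against 8/80 (10%) meets both conditions: a 20-point excess, Fisher p = 0.032. If 7.3 were read as plain Bonferroni over the looks (0.05/7 = 0.007, z-test), the false-stop rate would be 2.2%. Which section governs therefore matters.

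**SAE limb, counted alike.** The protocol gives no SAE rate. Assume 25% in both groups and SAE data on the same patients at each look. Requiring at least 20 points and p < 0.05 (z-test), the criterion is met in about 4% of studies. For SAE rates of 10%, 20%, 30% and 40% the figures are 1.0%, 3.2%, 4.0% and 4.6%. The 20-point condition holds down the effect of repeated looks here.

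**SAE limb, counted by attribution.** Keep 25% in the normal group and add an excess in the impaired group that arises only from attribution:

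| Attribution-only excess | Criterion met at some look |
|---|---|
| 0 points | about 4% |
| 2 points | about 6% |
| 5 points | about 11% |
| 10 points | about 27% |

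A second set of assumptions shows how such an excess can arise. Let objective SAEs have rate a = 15% and third-class events true rate b in both groups, each third-class event being counted with probability c. The counted rate is 1 − (1 − a)(1 − b·c).

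- b = 10%, c = 0.8 (impaired) vs 0.2 (normal): 1 − 0.85 × 0.92 = 21.8% vs 1 − 0.85 × 0.98 = 16.7%; false difference 5.1 points; criterion met in 9%.
- b = 20%, same c: 28.6% vs 18.4%; 10.2 points; 26%.
- c = 0.8 vs 0.4: 3.4 points and 7% (b = 10%), or 6.8 points and 15% (b = 20%).

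With every event counted (c = 1 in both groups) the false difference is 0.

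**AE wording.** 6.1.1 defines no AEs and 6.3.1 collects none, yet 6.2.1 compares their incidence. The stopping rule in 7.5 names only SAEs, so the conflict does not affect it.

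**The case against.** **On the SAE count.** Two of the three classes are objective. The third accepts mere suspicion, in either group, and 6.2.1 expects attribution to be difficult, so under-counting in both groups is possible. A reader might infer that a given stroke will certainly be an SAE after an impaired heart and not after a normal one; the text makes this possible, not certain. The protocol has no SAE rate and no attribution rate, so no percentage above is an estimate for this study, and small biases matter little (about 6% at 2 points). Meeting the criterion is also not the same as stopping. All of this stands. It limits the size of the claim. It does not restore comparability, because the counting rule still depends on the grouping variable.

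**On the looks.** The rule can stop only for harm; there is no early claim of non-inferiority. The 10-point condition equals the margin and already reduces false stops, and 7.5 also asks that the excess be confirmed, without saying how. Without an independent committee, a sponsor may reasonably prefer a rule that triggers easily. A stricter boundary has a price: Fisher at 0.02 cuts detection of a true 10-point excess from 65% (Fisher as written; 67% by chi-square) to 56%, a loss of 9 to 11 points. This stands too, so a stricter boundary is a trade-off and not a correction. A reader might also infer that seven unadjusted looks inflate the type I error of the non-inferiority conclusion. They do not: these looks provide no route to that conclusion.

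**On multiplicity.** 7.3 could be read as covering the looks, but 7.5 writes the threshold as p < 0.05 and does not refer to 7.3. The conflict is in the protocol itself, whatever an analysis plan may add.

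**Conclusion.** The SAE comparison is not like for like. This rests on the text alone: the third class in 6.1.2 is conditional on suspected donor cardiac function, 6.2.1 and 7.5 compare groups defined by that function, and 6.5 confirms unblinded conduct without an independent committee. The likely direction is over-counting in the impaired-heart group. The size is unknown. The rise from about 4% to about 6%, 11% or 27% for 2, 5 or 10 points is illustrative and assumes a 25% SAE rate; it is a chance of meeting a discretionary criterion, not of termination.

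The repeated looks carry a cumulative false harm-stop chance of about 5.5% (Fisher) to 7% (chi-square), assuming 10% events in both groups and 20% impaired hearts. That may be acceptable for safety, but the protocol should state it, and should say how 7.3 relates to 7.5. The AE conflict is editorial.

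**What to change.** (a) In 6.1.2 and 6.2.1, for the between-group and interim comparison, count third-class events by event type and time window alone, identically in both groups. Record suspected relation to donor heart function as a separate field. The cost is wording and a few more SAE forms, mainly for recipients of normal hearts.

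(b) In 7.5, name the test, give the cumulative false-stop rate of the rule (about 5.5-7%, depending on the test) and say whether 7.3 applies to the looks. This costs wording only. A stricter boundary is optional; if one is chosen, report the loss of detection beside the gain (Fisher at 0.02: false stops about 3%, detection about 56%).

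(c) Reconcile 6.2.1 with 6.1.1 and 6.3.1 by removing AEs from the interim comparison. This is an editorial change.

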## 2. Risk-benefit evaluation

Today, patients are transplanted with donor hearts with impaired function. In the vast majority of cases, such transplantations occur according to the recommendations given in this study (section 5.1). In retrospective data, these patients do not have worse outcomes in the short- or long-term, also in adjusted data. However, in retrospective studies we do not have control of all covariates and there may be factors that the responsible surgeon took into account which could not be measured. Thus, there is a conceivable risk that patients have an increased risk for complications, if the utilization of such hearts would be more liberal.

The overall benefit of utilizing donor hearts with impaired function is the recipient's shorter time waiting for an organ. For the recipient, this means a shorter time on the waiting list. While waiting for transplantation it is not uncommon that cardiac function deteriorates. The patient might be in need of mechanical assist and in worst case, the patient dies. In addition to the reduction of these risks, the patient's time with a disabling disease is decreased.

The study will continuously evaluate the results to find an increased risks for the group who has received a heart with impaired function. In such cases, the study will be prematurely terminated.

From a larger perspective, more available heart donors will allow patients to be more liberally accepted for transplantation. In the long-term, we hope that this can change the guidelines for which patients are relevant for transplantation. Our hope is also that fewer patients will need mechanical assist, a treatment that is expensive and limits daily activities.

This study will not expose heart recipients to any examinations or examinations other than those performed as part of clinical follow-up, which means that there is no additional suffering for the patient in the study follow-up.

Based on ours and others' retrospective data, there is no increased risk from receiving a heart that has impaired function. The guidelines set up in this study are based on studies of 1400 reported patients. Based on the state of knowledge today, we expect that these heart recipients will not have an increased risk for complications or death. The benefit for the patients is that they will receive their transplantation faster, which is a favorable factor. Taken together, we estimate that the potential benefit outweighs possible risks.

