#### **SAE Monitoring**

- Serious Adverse Events (SAEs) are monitored during the first 28 days post-transplantation. SAEs can be repeated if multiple events occur in the same patient.

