## 7.2. Statistical analyses

### 7.2.1. Statistical methods

The primary variables will be analyzed with binary logistic regression. The primary outcome variable will be incidence of death, re-transplantation or need of long-term mechanical assistance within one year after transplantation. The primary explanatory variable is incidence of cardiac dysfunction in the donor, defined as regional hypokinesia and/or ejection fraction < 50%. The analysis will be adjusted for age of recipient, age of donor, need of mechanical assistance before transplantation and "urgent call" status of transplantation.

For statistical significance, the p-value must be  $> 0.05$ .

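### The first between-group SAE comparison waits for one-year outcomes although SAEs are registered for only 28 days, so it comes about 11 months later than it could

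*Protocol*

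**What the plan says.** All references are to the protocol.

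- **Trigger (7.5).** "Interim analysis will be performed after 100 patients have been analyzed for the primary outcome", and again after each further 50 such patients. No other trigger is given.
- **Primary outcome (7.2.1).** "incidence of death, re-transplantation or need of long-term mechanical assistance within one year after transplantation".
- **SAE criterion (7.5).** "An increased incidence of SAE of at least 20 absolute percent as well as statistical significance" at p < 0.05 can end the study. It stands in the same section as the primary-outcome criterion and has no timing of its own.
- **Place of the SAE comparison (6.2.1).** "The incidence of AE and SAE between groups will be analyzed in interim analyses". Section 6.4 likewise ties discontinuation for an SAE excess to the interim analysis.
- **SAE window (4.2, SAE Monitoring).** "Serious Adverse Events (SAEs) are monitored during the first 28 days post-transplantation". The visit schedule agrees.
- **Risk-benefit argument (Section 2).** "The study will continuously evaluate the results to find an increased risks" in the group given impaired hearts.
- **Other safeguards.** SAEs reach the sponsor within 24 hours (6.3.2) and each is analysed for a link to donor heart function (6.2.1). The sponsor may stop the study for many severe events (4.4). No independent safety committee is planned (6.5).

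**The concern.** The SAE criterion is the plan's early-warning rule. It covers death within 28 days and mechanical support beyond 24 hours, both known within a month of surgery. Yet the comparison that would show an excess in recipients of impaired hearts is released only when a fixed number of patients have one-year results, which it does not use.

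At stake is how many more impaired hearts are transplanted before the two groups are first compared on early harm. Section 2 concedes a possible risk from more liberal use of such hearts and relies on ongoing evaluation as the safeguard. Section 6.2.1 expects SAEs to be hard to attribute to donor heart function case by case, so the group comparison carries much of the weight.

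**Working it through.** **Inputs from the protocol.** Looks at 100 patients and then every 50 (7.5); one-year outcome window (7.2.1); 28-day SAE window (4.2); 445 patients needed and 500 planned, 20% with dysfunction (7.4); study period Q2 2020 to Q2 2027 (Synopsis).

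**Assumptions.** Accrual is even. It takes 5 to 7 years; 6 years corresponds to keeping the last year of the study period for follow-up.

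**The plan's own figure.** The protocol states neither alpha nor power. With one-sided 0.025, 80% power, 90% event-free in both groups, a 10-point margin and 1:4 allocation, the dysfunction group needs (1.960 + 0.842)² × 0.90 × 0.10 × (1 + 1/4) / 0.10² = 88.3, so 89, and 89 / 0.20 = 445. The stated size is reproduced. It enters below only through the accrual rate.

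**Lag.** 365 − 28 = 337 days; 337 / 30.44 = 11.1 months.

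**Transplants during the lag.** With N patients over Y years, the yearly rate is r = N / Y. Transplants in the lag = r × 337/365, and 20% of these have impaired hearts. At the first look, transplants done = 100 + r with the one-year trigger and 100 + r × 28/365 with a 28-day trigger.

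| N | Years | r per year | Done, one-year trigger | Done, 28-day trigger | Transplants in lag | Impaired |
|---|---|---|---|---|---|---|
| 445 | 5 | 89.0 | 189 | 107 | 82 | 16 |
| 445 | 6 | 74.2 | 174 | 106 | 68 | 14 |
| 445 | 7 | 63.6 | 164 | 105 | 59 | 12 |
| 500 | 5 | 100.0 | 200 | 108 | 92 | 18 |
| 500 | 6 | 83.3 | 183 | 106 | 77 | 15 |
| 500 | 7 | 71.4 | 171 | 105 | 66 | 13 |

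With 6 years of accrual the first look falls 100/r + 1 = 2.2 to 2.35 years after the start. With a 28-day trigger it would fall at 100/r + 28/365 = 1.3 to 1.4 years.

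**Last looks.** Under the one-year trigger, the look at 400 (N = 445) or at 450 (N = 500) falls after accrual has ended in every row. An SAE stop there could protect no new recipient.

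**Does more 28-day data make the rule more likely to be met?** Take the first look with N = 445 over 6 years. If only the 100 patients with one-year outcomes enter, the groups are 20 and 80. If all 174 transplanted patients enter, they are about 35 and 139. The chance of an observed excess of at least 20 points together with pooled z > 1.96 follows by exact enumeration of two binomials. The protocol gives no SAE rates and 7.5 names no test, so both are assumptions.

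| SAE rate, impaired vs normal | 20/80 | 35/139 |
|---|---|---|
| 55% vs 25% | 73% | 86% |
| 45% vs 25% | 43% | 49% |
| 40% vs 25% | 28% | 28% |
| 30% vs 10% | 51% | 48% |
| 25% vs 25% (false alarm) | 3.0% | 0.9% |

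A few of the 174 would not yet have 28 complete days. With 34/136 the first row gives 85% instead of 86%.

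**The case against.** Four stronger readings are tempting, and the protocol does not support them.

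**That every look is 11 months out of date.** Section 7.5 does not confine the SAE comparison to patients with one-year outcomes. If each look uses the 28-day data then at hand, later comparisons are current and come every 50 / r years (7 to 8 months with 6 years of accrual), the same spacing as under a 28-day trigger. Only the first is then delayed. A statistical analysis plan, not available here, may settle which patients enter.

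**That early harm goes unexamined.** Each SAE reaches the sponsor within 24 hours and is analysed for a link to donor heart function. The study is unblinded, mortality is checked at 3 and 6 months, and 4.4 lets the sponsor stop without an interim look. This is real ongoing review and could be what Section 2 means. But 4.4 gives no threshold, schedule or comparison, and case review does not compare groups.

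**That the fix reliably raises the chance of detecting harm.** It does so for a large excess. For a true excess of 20 points or less the gain is small, absent or negative. The steadier benefit is fewer false alarms.

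**That the study causes the extra exposure.** Participation does not affect organ allocation (4.1) and the surgeon decides on acceptance. This weakens the point without removing it, since the protocol issues acceptance recommendations and Section 2 concedes a risk from more liberal use.

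One practical objection also stands. With a start in Q2 2020 and 6 years of even accrual, the first look falls in the second half of 2022, and this protocol version already cites a 2023 guideline. The first look has probably passed.

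**Conclusion.** The point holds for the timing of the first SAE comparison. As written, it comes 337 days later than 28-day data on 100 patients would allow. That is about 59 to 92 further transplants, 12 to 18 with impaired hearts, under even accrual of 445 to 500 patients over 5 to 7 years. If deaths count as analysed as soon as they occur, the lag shortens to about 10 months.

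For later looks the fault is an unstated analysis set. Should the SAE comparison be limited to patients with one-year outcomes, each look would ignore about a year of available 28-day data; otherwise it would not.

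Section 2 is better described as unmatched than as flatly contradicted: single-case review is continuous, but no specified group comparison is. Because the first look has probably passed, the practical value lies in the remaining looks and in reconciling Sections 2, 4.4, 6.4 and 7.5.

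**What to change.** In 7.5, give the SAE comparison its own trigger: 100 transplanted patients with complete 28-day data, then every further 50. State that at any look it includes all patients with complete 28-day data. Reword Section 2 to name this schedule together with the single-case review. Leave the stated SAE thresholds as they are. If early looks have passed, apply the change to the remaining ones.

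The text cost is two sentences in 7.5, one in Section 2, and a short SAE table per look. There are two downsides:

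- Interim work runs on two timelines.
- If SAE tests are run at both triggers, there are more unadjusted tests at p < 0.05. With N = 445 the looks at 100, 150, …, 400 number 7, so up to 14 SAE tests instead of 7. The 20-point requirement limits the false alarms, and the rule permits termination without requiring it. Testing SAEs only at the 28-day counts keeps the number at 7.
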